##### Data collection

Step 1a: In 2017, all institutions providing SAPV in Germany were asked to submit data to the guide for hospice and palliative care services (Wegweiser “Hospiz- und Palliativversorgung”), an online data base provided by the DGP. The guide is based on voluntary information given by institutions and contains data of 270 SAPV providers. As there is no existing comprehensive list of SAPV providers in Germany, the guide contains the largest existing list of SAPV teams. Step 1b: The contracts will be analyzed regarding their differences in regulation. In order to validate information and assess different practices, interviews with local SAPV providers or stakeholders, who are involved in policy making, are conducted. Step 2: Coded patient data is extracted through two widely used electronic medical records (EMR) software solutions in Germany: PalliDoc (StatConsult) and ISPC (Smart-Q). Data assessment is based on the consented data set for a nationwide hospice and palliative care registry. Few additional items will be assessed (number of visits, number of hospital additions, socioeconomic status). SAPV teams ask all patients admitted to SAPV during six month for permission for data extraction.

##### Data analyses

Step 1a/1b: Structural and contract variables will be analyzed descriptively. Step 2: Hierarchical multilevel models will be used to analyze associations between structural predictors and the patient and care parameters.

#### Subproject 2

Quality assurance in SAPV – a quantitative collection of data from patients´ perspective.

##### Hypotheses

Patients´ perspective on quality of care in SAPV is correlated to structures and processes of SAPV teams.

##### Method and Design

With a questionnaire, called QUAPS [22], developed to assess quality of care with SAPV, patients report their perspective on quality of symptom control, processes of care and results. In addition, IPOS (Integrated Palliative care Outcome Scale) is assessed at the time of inclusion (IPOS baseline) and about 3–14 days after inclusion (IPOS follow-up).

##### Study population

Data from 25 consecutive patients from 50 SAPV teams covering the 17 KV regions are collected over a maximal period of 6 months, resulting in data from 1250 patients.

##### Data collection

Data of all patients cared for by the SAPV team within the period are collected with subproject 1 via export from the EMR system (PalliDoc or ISPC). The IPOS and QUAPS questionnaires are collected by the local SAPV team and sent in a closed envelope to the study center.

##### Data analyses

Data analysis is descriptive. IPOS baseline data are compared to IPOS follow-up data. QUAPS data are compared between SAPV teams. In a further step, data of subproject 2 are analyzed for their association with data on structures and processes of SAPV teams, collected by subproject 1.

#### Subproject 3

Beneficial and inhibiting factors for a successful performance of SAPV teams from the perspective of SAPV team members and network partners.

##### Hypotheses

The self-perception, working strategies, team cultures and organizational structures of SAPV teams are influenced by patient-, payment-, organization-, region- and structure-related factors.

##### Method and Design

We develop and carry out problem-centered interviews within the framework of an ethnographic qualitative study design by means of on-site field studies based on grounded theory. The aim of grounded theory research is not only to “uncover relevant conditions but also to determine how the actors under investigation actively respond to those conditions and to the consequences of their actions” [30]. Basic elements of a research approach according to the grounded theory are the following: Data analysis begins with the first bits of data available, further collection of data is based on the ongoing process of data analysis all along the duration of a research project. Any outcome of the data analysis such as concepts and categories are constantly contrasted and compared, e.g. similar situations discovered in various interviews are compared. This is also an important means to evaluate the findings. Thus, concepts discovered at the beginning of the research process are likely to have completely changed till the end of the research.

##### Study population

The study population is centered on 10 SAPV teams and their environment, i.e. their external network partners as well as other local care providers - if possible even those who deliberately chose not to cooperate with the SAPV team. The selection is determined by various categories such as size of team, economic prosperity of region, population density, organizational contexts, etc. The aim is to gather information from a broad spectrum of teams and to contrast certain categories as much as possible, for example a contrast between teams in rural vs. teams in urban areas or completely autonomous teams vs. teams embedded in a wider organizational context like hospitals or hospices.

##### Data collection

The data is being collected mainly by means of qualitative, problem-centered interviews. Interviews are being conducted on-site with SAPV team members such as team-managers, physicians, palliative care nurses, counselors and external network partners like GPs, retirement homes, palliative care units in hospitals, pharmacies and medical stores. Topics of the interview guidelines include daily working habits, characteristics of patients and team dynamics as well as future and structural effects of SAPV in the local area. The research-team also uses the technique of field notes to provide a wider context around the interviews.

##### Data analysis

We are conducting a qualitative analysis within the grounded theory framework. This involves inductive and deductive analysis of interview data.

#### Subproject 4

General Practitioners‘care for palliative patients within and outside SAPV (GPs‘perspective).

*Hypotheses:* The self-perception and tasks of GPs in palliative care in general and the prescription of SAPV by GPs in particular are determined by patient-, physician-, qualification-, payment-related and other environmental (i.e. palliative infrastructure) factors.

##### Method and Design

Based on a literature search for criteria to measure the role of the GP in palliative care, the following steps are part of the project: Step 1: Definition and evaluation of corresponding questions for the qualitative analysis of interviews with GPs in cooperation with subproject 3 and in preparation for the subsequent quantitative analysis. Step 2: Quantitative analysis of a GP survey. Step 3: Synthesis of the results of the qualitative and quantitative analysis as well as the claims data analysis (subproject 5) with the aim to derive criteria for a systematic description of the GP’s involvement in AAPV and SAPV. The development of the questionnaire (step 2) is based on a literature search and semi-structured interviews with GPs and palliative care specialists. Pretests are performed before finalizing the questionnaire.

##### Study population

Random sample of 6000 GPs in the federal states of Bavaria, Berlin, Hesse, Lower Saxony, Saxony-Anhalt, Schleswig-Holstein, Thuringia and Westphalia-Lippe as a part of North Rhine-Westphalia. The selection is based on the structure of regional SAPV contracts as well as the number of inhabitants and size to represent the heterogeneity of SAPV in Germany.

##### Data collection

The GP address data are collected via free-access internet portals or obtained from the Regional Association of Statutory Health Insurance Physicians. The postal questionnaire is addressed to 750 GPs in each survey area. Survey data will be transcribed into a database electronically. Within a standardized, quantitative study design, a postal survey with 750 GPs from eight regions each is performed in 2018. The regions were selected in consideration of the different structural characteristics of SAPV in Germany, evaluated in subproject 1, to represent differences in the regions. The expected response rate is 20% (*n* = 1200).

##### Data analyses

We will conduct a descriptive analysis of quantitative variables and will also perform univariate and multivariate regression analyses on the association between independent and dependent variables.

#### Subproject 5

SAPV in comparison to other types of palliative care: patient characteristics and resource utilization (payer’s perspective).

*Hypotheses:* The type, extent and quality of palliative care a patient receives during the last months before death differs according to patient characteristics as well as regional structures of palliative care provision.

##### Method and Design

We perform a retrospective cohort study in a cross-sectional design with a subgroup analysis. By means of pseudonymized master data, people insured with the health insurance fund BARMER who died in 2016 (study population) are identified. It will be determined if patients received palliative care and if yes, what level of palliative care with regard to general or special palliative care, in- or outpatient palliative care, or combinations thereof, they received within the last six months before their death. On this basis, we will assign the patients to the study cohorts.

##### Study population

About 95,000 adults throughout Germany, insured, with the health insurance fund BARMER and time of death in the year 2016.

##### Data collection

Pseudonymous individual claims data (according to §§ 284, 295, 300, 301, 302 of the Fifth Book of the Social Code, SGB V) are made available via the Scientific Data Warehouse of the health insurance fund BARMER. Additional variables and value lists, which are considered relevant for the planned investigation (i.e. specific billing codes for AAPV and SAPV as well as hospices care data), were supplemented. Relevant periods of observation of received health insurance fund services include the last six and three months before death, the time period between months 12 and seven before death is defined as pre-observation period. The assignment of patients to cohorts and subgroups is executed by means of defined outpatient billing codes or hospital-based operation and procedure codes (OPS). We use preexisting indicators and – under consideration of the limitations of claims data - develop and quantify new and eligible indicators to describe distinct types of palliative care, their utilization and their quality of care. The study population will be characterized by socio-economic, administrative diagnoses and other care-specific attributes. In addition, we will calculate measures aimed at describing the quality of palliative care based on variables available in claims data.

##### Data analyses

Outcome measures and patient characteristics will be described statistically for each cohort and region. For the comparison of outcome measures between cohorts and regions we intend to use multivariate regression analyses.

## Discussion

Recent analyses in Germany focused mainly on the description of (regional) SAPV structures and utilization [12–15, 17]. A nationwide assessment of SAPV from different and relevant perspectives has not yet been conducted. To provide this, SAVOIR addresses: [1] the structural characteristics of SAPV and their impact on patient care, [2] the quality of care from the perspective of patients, [3] the quality of care from the perspective of SAPV teams, hospices, ambulatory nursing services, nursing homes and other care givers, [4] the content and extent of care from the perspective of GPs and [5] the health insurance fund as a payer. The comprehensive, nationwide data assessment in the SAVOIR study uses different perspectives and data sources as well as both quantitative and qualitative methods. This allows us to identify the current conditions and special needs in palliative care from patients, relatives, care providers and payers in Germany. Subsequently we will compare different care models and provide an overview of SAPV provision in Germany and moreover we will provide an in-depth analysis of differences - even if we will not be able to take the entirety of differences into account. Based on these findings, factors related with high quality of care in SAPV will be identified.

Although SAVOIR uses multi-method and transdisciplinary approach with unique advantages, clinical research in patients with an advanced and life-limiting disease remains challenging, i.e. with regard to suitable research methods as well as the participation of healthcare professionals and the recruitment of patients [31–34].

According to the different research strategies in each subproject, we are conscious of the following limitations:

**Subproject 1:** In step 1a, teams may not provide their real personnel structures, but rather a socially desirable version. The interviews were conducted via phone, which may increase this effect. The regulatory contracts may not cover the “real care provision”, as there may be regional differences that were not captured in the interviews and that we are unaware of. Some regions have model contracts, but specific characteristics like financial reimbursement may still vary between teams. To assess patient care, we use clinical routine data. While our prospective assessment enables us to give the teams information about the extracted data in advance and thus provide a better data quality, clinical routine data still is difficult to interpret. The variables used may be differently understood by those who document them and thus result in various interpretations within and between collecting SAPV teams.

**Subproject 2:** Questioning palliative patients and their relatives can only be pursued under several limitations: Patients are often in a poor general condition, participation in research is an additional burden for them and palliative care teams are often not experienced in clinical research and are reluctant to address participations. A specific challenge is given by the fact that life expectancy in SAPV patients is often limited to days or few weeks and treatment ends in most cases with the death of the patient. Therefore, in contrast to most other types of care, it is not possible to approach patients at the end of SAPV treatment. On the other hand, patients have to have experienced a certain time of SAPV care before they can report on its quality. Therefore, there is only a small time window to obtain patient-reported information on quality of SAPV care [35]. This may reduce the sample size and those participating may be a selected group of relatively “healthy” patients. However, pilot testing has revealed that the chosen approach will result in a sufficient number of data sets. Therefore we conduct a multi-method design, collecting treatment data of all patients agreeing to participate in subproject 1 over the time of recruitment for subproject 2.

**Subproject 3:** The field survey may lead to self-selection of participating SAPV teams: We expect that SAPV teams interested in research and improvement of palliative care will be more likely to participate. A measure to prevent self-selection of SAPV teams is the purposeful selection of participants via a set of various criteria such as the size of the team, economic prosperity of region, population density, organizational contexts, etc. Furthermore SAPV teams themselves select external network partners for the interviews. We expect that only external network partners are chosen for participation who are highly motivated, interested in palliative care and have positive experiences in working together with SAPV teams. Especially GPs with a more reserved attitude towards SAPV are unlikely to participate. This aspect is methodologically reflected during the data analysis.

**Subproject 4:** In the GP survey we have to deal with the fact that GPs more interested, qualified and/or experienced in end-of-life care might be more willing to participate in the survey than others. Therefore, we request information on the extent, experience and qualification in terms of palliative care from the GPs to be able to determine the impact of these factors on the results.

**Subproject 5:** Though the BARMER made great efforts to collect all relevant data on SAPV and to transfer it into the Scientific Data Warehouse, the claims data base on SAPV will not be fully complete by the end of the project and may not cover all existing health services within SAPV in Germany. The data do not contain full information on the qualification levels of care providers necessary to finer differentiate between levels of palliative care such as palliative care approach and general patient care. Apart from many advantages in analyzing claims data, their information value for the measurement of quality of care is restricted due to the lack of clinical and patient reported data.

To sum up, SAVOIR – consisting of five subprojects – will provide important information on the complex and regionally varying structures, processes, extent and quality of SAPV in Germany and the factors which determine the quality of SAPV from the different perspectives of stake-holders involved. We aim at deriving recommendations to further develop the SAPV directive. The results will add valuable knowledge on starting points to improve outpatient palliative care, mainly in Germany, that might be applicable for other countries, too.

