**Methods:**

The processes, content and quality of SAPV will be evaluated from the perspectives of patients, SAPV teams, general practitioners and other care givers and payers. The influence of different contracts, team and network structures and regional and geographic settings on processes and results including patient-reported outcomes will be analyzed in five subprojects: [1] structural characteristics of SAPV and their impact on patient care, [2] quality of care from the perspective of patients, [3] quality of care from the perspective of SAPV teams, hospices, ambulatory nursing services, nursing homes and other care givers, content and extent of care from [4] the perspective of General Practitioners and [5] from the perspective of payers.

The evaluation will be based on different types of data: team and organizational structures, treatment data based on routine documentation with electronic medical record systems, prospective assessment of patient-reported outcomes in a sample of SAPV teams, qualitative interviews with other stakeholders like nursing and hospice services, a survey in general practitioners and a retrospective analysis of claims data of all SAPV patients, covered by the health insurance fund BARMER in 2016.

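### Subproject 5 defines its cohorts by billing codes that the protocol says are incomplete for SAPV, so missed SAPV patients fall into the comparison cohorts and uneven capture can look like regional under-supply

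*Protocol article*

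**What the plan says.** The study population of subproject 5 is "About 95,000 adults throughout Germany" who were insured with BARMER and died in 2016 (Subproject 5, Study population). Its Method and Design section sets the classification task for the last six months of life: "It will be determined if patients received palliative care and if yes, what level of palliative care". It continues: "On this basis, we will assign the patients to the study cohorts".

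The Data collection section gives the only assignment rule: "The assignment of patients to cohorts and subgroups is executed by means of defined outpatient billing codes or hospital-based operation and procedure codes (OPS"). It adds that code lists for general and specialised outpatient palliative care, and hospice data, were supplemented. No category for unknown SAPV status is named.

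The Data analyses section then states: "Outcome measures and patient characteristics will be described statistically for each cohort and region". Cohorts and regions are to be compared by multivariate regression.

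The limitations paragraph for subproject 5 in the Discussion says that, despite the fund's efforts, "the claims data base on SAPV will not be fully complete by the end of the project and may not cover all existing health services"; the sentence goes on to specify services within SAPV in Germany. It gives no capture rate, no pattern by region and no analytic response.

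The abstract (Methods) describes this component as "a retrospective analysis of claims data of all SAPV patients, covered by the health insurance fund BARMER in 2016".

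**The concern.** The variable that is known to be incomplete is the one that defines the exposure. Under the only rule given, a decedent who received SAPV but has no captured SAPV code cannot enter an SAPV cohort. That person is counted with those who had other palliative care or none.

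Two consequences follow:
- **Regional uptake is understated wherever claims are missing.** If the gaps are uneven, a shortfall in data capture cannot be told apart from a shortfall in care.
- **Comparison cohorts contain some SAPV patients.** This pulls the SAPV and comparison results towards each other.

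Regional variation is part of the stated aim of subproject 5. The Background hopes the claims data may give hints of over-, under- and missupply, and the findings feed recommendations on the SAPV directive.

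Separately, the abstract's account of the population does not match the body of the article.

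**Working it through.** The protocol states no capture rate, cohort size or power for subproject 5, so there is no figure of its own to reproduce. The check is an illustration.

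**Inputs from the protocol**
- Decedents: N = 95,000 (Subproject 5, Study population).
- KV regions: 17 (Design and setting). The mean region has 95,000 / 17 = 5,588 decedents.
- SAPV uptake: 6% of all deaths in Germany in 2016 (Background).
- Estimated need for specialist palliative care at home: 10% of dying patients (Background).
- More than 290 SAPV contracts (Background).

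**Assumptions**
- The 6% national rate holds among BARMER decedents, which gives 95,000 × 0.06 = 5,700 true SAPV patients.
- A fraction c of SAPV patients has at least one captured SAPV code. A range is shown.
- Tests are two-sided at 0.05.

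**1. Uniform gaps.** Observed uptake is c × p.
- The ratio between two regions is cp₁ / cp₂ = p₁ / p₂, so relative contrasts are preserved.
- The difference is c(p₁ − p₂), so absolute contrasts shrink.
- The overall level falls. At c = 0.8, 6% is seen as 4.8%, and the apparent shortfall against the 10% benchmark grows from 4.0 to 5.2 percentage points.
- No false regional pattern arises.

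**2. Uneven gaps.** Take two mean-size regions with identical true uptake of 6%, one with full capture and one with capture c:

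z = (0.06 − 0.06c) / √[(0.06 × 0.94 + 0.06c(1 − 0.06c)) / 5,588]

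At c = 0.8: z = 0.012 / √[(0.0564 + 0.045696) / 5,588] = 0.012 / 0.00427 = 2.81.

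The chance of a falsely significant gap is approximately Φ(z − 1.96).

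| Capture in second region | Observed uptake | z | Chance of a significant artificial gap |
|---|---|---|---|
| 90% | 5.4% | 1.37 | 28% |
| 80% | 4.8% | 2.81 | 80% |
| 70% | 4.2% | 4.33 | 99% |

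**3. Contamination of comparators.** Missed SAPV patients number m = 5,700(1 − c).

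In the whole group without an SAPV code, their share is m / (95,000 − 5,700c). At c = 0.8 this is 1,140 / 90,440 = 1.3%. It is 0.3% at c = 0.95 and 3.1% at c = 0.5.

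For a smaller comparator of true size n, suppose all missed patients land there. The share is then f = m / (n + m). At c = 0.8:
- cohort of 10% of decedents (assumed): 1,140 / (9,500 + 1,140) = 10.7%;
- cohort of 20% of decedents (assumed): 1,140 / (19,000 + 1,140) = 5.7%.

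If missed and captured SAPV patients have similar outcomes, the observed contrast is (1 − f) times the true one.

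**4. Abstract against body.** The abstract speaks of all SAPV patients covered in 2016. Design and setting, and the Method and Design and Study population sections of subproject 5, define insured persons who died in 2016, with or without SAPV. The body is narrower (decedents only) and also wider (includes people without SAPV). The Discussion adds that SAPV capture is incomplete.

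**The case against.** The strongest reply is that this is a condensed article. Code definitions, handling of misclassification and sensitivity analyses commonly sit in a full protocol or analysis plan, and the limitation is openly disclosed. The authors also supplemented the code lists, cite good practice for secondary data analysis, plan plausibility and integrity checks, and have the fund as a partner. This counts against any picture of carelessness. However, none of these measures is a correction for missing SAPV claims, and the Discussion says gaps remain after the fund's efforts. What is criticised is a stated assignment rule set against an admitted defect in its input.

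Several stronger readings are tempting and are not supported:
- **That capture gaps will produce false regional under-supply.** This needs capture to differ by region. No section says it does. The number of contracts, and the remark in the subproject 1 limitations that reimbursement may vary between teams even under model contracts, make it plausible only.
- **That every gap loses a patient.** The limitation speaks of services within SAPV. A patient with some services unrecorded but one SAPV code captured could still be classified correctly; utilisation would then be understated, not cohort membership.
- **That the protocol declares the absence of a code to mean the absence of SAPV.** It does not say so in words; this is the effect of the only rule given.
- **That the comparison cohorts are seriously contaminated.** Against everyone without an SAPV code the share is small.
- **That detecting over- or under-supply is a formal aim.** The Background says only that hints might be found.

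The abstract mismatch is a separate, minor wording fault and is no evidence of misclassification.

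**Conclusion.** The point holds in a conditional form. As written, SAPV patients without any captured SAPV code are placed in non-SAPV cohorts, and the planned comparisons have no stated means of separating missing claims from missing care. If capture varies by region or contract, this can appear as regional under-supply; if it is uniform, only the overall level and absolute differences are affected.

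The size is unknown, because capture rates, cohort shares and uptake among this fund's decedents are all assumed. A 10% shortfall in one mean-size region would usually go unnoticed, whereas 20% or 30% would usually be declared a real difference. Dilution of the SAPV contrast is minor against the whole group without an SAPV code and could matter for small comparators. The abstract's population statement is wrong whatever the capture rate. The plan should be changed, but its national analysis is not invalidated.

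**What to change.** 1. With the partner fund, establish and report for each KV region, and by contract where possible, whether SAPV claims are captured. The fund is the natural source: nothing in the protocol shows that the contract inventory of subproject 1 (step 1b) records billing codes, although it may help to list the contracts to be checked.
2. Keep the national analysis. Add a sensitivity analysis of the regional comparisons and of SAPV versus other care, restricted to regions with verified capture. Elsewhere, either class decedents without an SAPV code as SAPV status unknown, or give bounds over a stated range of capture.
3. Make any conclusion on regional under-supply conditional on that analysis.
4. Correct the abstract to say that the analysis covers insured persons who died in 2016, with SAPV identified from recorded claims.

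The cost is a capture check, some extra analysis and one corrected sentence. The downside is reduced regional coverage in the sensitivity analysis. Removing regions from the main analysis would give up national coverage and is not needed.
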